## Abstract

**Background:** Osteoporosis (OP) patients are usually asymptomatic until osteoporotic fractures occur, which makes early diagnosis and prevention difficult, and the associated fractures secondary to OP could be preventable with appropriate management. Therefore, early identification and relevant evidence-based management of OP could guide the prevention of subsequent fractures. This study will investigate the prevalence of OP and the incidence of osteoporotic fractures in Beijing community residents to further explore the related risk factors and put forward suggestions for people aged 45–80 years old.

**Methods:** Over 2 years, this study will conduct an OP screening and a prospective follow-up in the Beijing community to investigate the incidence of osteoporotic fractures. The study will undertake bone mineral density detection, collect biological samples, and record information via questionnaires.

**Discussion:** The study aims to investigate the potential risk factors for osteoporosis and explore syndromes from traditional Chinese medicine that are associated with this condition based on large samples from the Beijing community. Data on the incidence of osteoporotic fractures among community dwellers in Beijing over the two-years will be available on the Chinese clinical trial registry: ChiCTR-SOC-17013090.

## Introduction

Osteoporosis (OP) is caused by changes in bone microstructure and decreases in bone strength (1, 2). As society has aged, this condition has become a serious issue that affects the physical and mental health of many elderly people (3). The most devastating outcome of OP (4), osteoporotic fractures, also known as fragility fractures, can inflict heavy burdens on families and society more widely, leading to increased use of healthcare resources and economic costs in Asia (5, 6). In China, the annual number of cases of OP-related fractures will be ~5.99 million by 2050, with an estimated cost of $25.43 billion (7).

In recent years, an increasing number of countries have started to be more concerned about community-based public health programs (8–10). Typically, there is a large population with osteopenia or osteoporosis in the community, which are undiagnosed before fractures occur, meaning that community-based health programs for OP screening could be of great significance to residents. For instance, bone mineral density (BMD) and bone turnover marker testing are necessary to ensure preventive interventions to reduce risks for populations with low bone mass, especially postmenopausal women, and elderly men (11, 12). Therefore, community-dwelling middle-aged and elderly people are subjects for whom it is important to prevent and manage OP and its associated fractures.

On the other hand, OP is a chronic disease that has complex causes. Some risk factors have already been confirmed in interviews and community research (13–15). A cross-sectional study in northwestern China found that the prevalence of OP was 9.65% for postmenopausal women and 8.08% for elderly males according to the criteria of the World Health Organization (WHO), and the risk of OP may be associated with age and body mass index (16). However, the epidemiological findings of OP, osteoporotic fracture, and other potential influencing factors were not identical in the different regions (17). A lack of follow-up is common in the majority of community-based studies.

This prospective study will investigate conventional risk factors and relevant symptoms as reported in traditional Chinese medicine (TCM) in populations with a high risk of postmenopausal osteoporosis (18, 19). Based on the findings of this preliminary study, we will then conduct a further cross-sectional survey and a prospective follow-up study in the Beijing community. The present prospective study aims to investigate the prevalence of OP and the incidence of osteoporotic fracture in Beijing community residents to further explore the risk factors related to this condition and to put forward some rational suggestions for patients. This research on “Beijing community-based Osteoporosis and osteoporotic fracture screening: a cross-sectional and prospective study (beyond)” will provide reliable data for the prevention of OP and osteoporotic fractures among community-dwellers in the Beijing area.

## Materials and Methods

This is a community-based cross-sectional and prospective follow-up study. Based on the different economic conditions in Beijing, we will seek residents from several districts from people who respond to an invitation to participate. Then, the participants will be screened, based on predetermined inclusion and exclusion criteria, and an epidemiological investigation will be conducted. The investigation will gather data on BMD screening, biological samples, and questionnaire information. Each participant will be followed for at least 2 years to track incidences of osteoporotic fracture. Based on a power analysis, the required sample size will be at least 1,500 patients. A flow chart of the research process is shown in Figure 1.

**Figure 1 F1:**
[figure not shown]
Flow diagram of the study.

### Participant Recruitment

Due to the potential impact of different socioeconomic conditions on the bone mass of populations, this study will recruit participants in the central urban area (Chaoyang District, Beijing) and suburbs (Fengtai District, Beijing). The aim is to avoid the potential bias caused by economic circumstances, education, work, and other factors.

We will randomly select 2 to 5 communities across two administrative regions and then contact the local committee that represents community residents or health service departments. The researchers will work with community staff to post recruitment advertisements in community corridors, billboards, and other public places, which will explain the purpose of this study, testing project, and potential benefits for the participants who take part.

### Ethics and Registration

This study was approved by the medical ethics committee of Wangjing Hospital, China Academy of Chinese Medical Sciences (approval number: WJEC-KT-2017-020-P001) and registered in the Chinese Clinical Trial Registry (approval number: ChiCTR-SOC-17013090). The study will notify all participants or their legal representatives before they are asked to sign an “informed consent form” in accordance with the Helsinki Declaration.

### Diagnostic Criteria

According to the criteria outlined by the WHO and Chinese guidelines for the diagnosis and treatment of primary OP (20), T-score ≥-1 is defined as normal, T-score < −1 and > −2.5 is considered osteopenia, and T-score ≤-2.5 is considered OP based on bone densitometry.

TCM syndrome refers to the nature of a certain stage in the occurrence and evolution of osteoporosis and the specific internal and external environment of the individual/patient at that time. TCM treats a disease based on full consideration of the individual constitution, climatic and seasonal conditions, and environment. This is embodied in the term “giving a treatment on the basis of syndrome differentiation.” Syndrome differentiation is one of the most important factors in the practice of TCM and means diagnosing an illness as a certain syndrome based on analyzing specific symptoms and physical signs, which are collected by inspection of auscultation, olfaction, and palpation. Thus, TCM syndrome differentiation could be used as a method of patient stratification and could help in choosing the most appropriate patients for intervention, based on clinical information on different syndromes.

According to the guidelines on clinical practice for the treatment of primary OP in traditional medicine, the TCM syndromes presented by patients mainly include kidney-Yang deficiency syndrome, liver-yin, and kidney-yin deficiency syndrome, spleen-Yang, and kidney-Yang deficiency syndrome, and blood stasis and qi stagnation syndrome, all of which will be recorded in the present prospective study.

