### Inclusion and Exclusion Criteria

The inclusion criteria for this study will be as follows: (1) the individual has lived locally for more than 5 years; (2) female participants will ve aged between 45 and 80 years old (45 ≤ age < 80) and male participants will be aged 50 to 80 years old (50 ≤ age < 80); (3) a written informed consent form will be signed by the subjects, and the process of obtaining this informed consent will be ethical. Participants who suffer from mental illness, such as a mental deficiency, memory or thinking disorder, and who are unable to cooperate with investigators due to disability or lack of physical capacity will be excluded.

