### Collecting Clinical Information

All participants will complete a face-to-face paper version of the questionnaire and undergo a comprehensive physical examination. The questionnaire and examination will mainly assess the general characteristics of participants, menstrual status, menopausal age, number of pregnancies, number of births, education level, income level, history of smoking and drinking, history of previous illness and medication, number of falls, daily dietary habits, TCM syndrome, and so on. Information on various fractures, such as the number, cause, location, and therapeutic method, will be recorded in detail. The questionnaire will also include the International Physical Activity Questionnaire (21), the 1 Min Osteoporosis Risk Assessment Test of the International Osteoporosis Foundation (22), and the EuroQol 5-dimension instrument (23) to evaluate the physical activity and quality of life of participants.

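### The T-score classification has no menopausal limit and women enter from 45, so the female osteoporosis prevalence and the risk-factor comparison mix premenopausal and postmenopausal women

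*Protocol article*

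**What the plan says.** All references are to the protocol article.

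- **Diagnostic Criteria.** The rule is introduced with "According to the criteria outlined by the WHO and Chinese guidelines for the diagnosis and treatment of primary OP (20"). It has three bands (normal, osteopenia, OP), and for the lowest "T-score ≤-2.5 is considered OP based on bone densitometry". No limit by sex, age or menopausal status is given, and no other rule is offered.
- **Inclusion and Exclusion Criteria.** Women qualify if "aged between 45 and 80 years old", with 45 included. Men qualify from 50. Menopause is not a criterion.
- **Bone Density Screening.** T- and Z-values are recorded at each site. The Z-value has no stated use.
- **Collecting Clinical Information.** The questionnaire covers "menstrual status, menopausal age" and other reproductive history. None of it is tied to the diagnosis.
- **Introduction.** The one prevalence benchmark under the WHO criteria is from northwestern China: "the prevalence of OP was 9.65% for postmenopausal women and 8.08% for elderly males according to the criteria of the World Health Organization (WHO"). The aim is OP prevalence in residents of the Beijing community. The Abstract gives the age range as 45–80.
- **Data Management and Statistical Analysis.** Age, gender and comorbidities are named as examples of adjustment factors. Menopausal status is not named.

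**The concern.** Stage one is meant to deliver an OP prevalence and a set of risk factors. Under the printed rule, a premenopausal woman aged 45 or over is placed in the same three bands as a postmenopausal woman and counted with her. This has two consequences.

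First, the female prevalence becomes an average over two groups, weighted by however many premenopausal women answer the recruitment advertisements. It cannot be set beside the postmenopausal figure that the article itself cites, nor beside another study with a different mix.

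Second, the OP versus non-OP comparison among women partly becomes a comparison of menopausal status. Menopausal age, one of the factors collected, has no value for premenopausal women. They would drop out of any analysis of that factor or need an arbitrary code.

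The information needed to separate the groups is already collected but is given no role.

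**Working it through.** **What there is to reproduce.** The article forecasts no prevalence for this study. Its only design figure is a minimum of 1,500 participants, given without power, effect size or precision. That figure cannot be re-derived, and this point does not depend on it.

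**Inputs**
- p_post = 9.65%, postmenopausal women (Introduction; a study from another region).
- p_men = 8.08%, elderly males (same source).
- s = premenopausal share of women: not given; assumed 5–20%.
- p_pre = share of premenopausal women with T ≤ -2.5: not given; assumed 0–3%.
- For overall figures, half the sample is assumed to be men.

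**Step 1: pooled female prevalence against postmenopausal-only**

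Pooled = (1 − s) × p_post + s × p_pre, so the gap is s × (p_post − p_pre).

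| s | p_pre = 0% | p_pre = 3% | gap from 9.65% (points) |
|---|---|---|---|
| 5% | 9.17% | 9.32% | 0.48 to 0.33 |
| 10% | 8.69% | 8.99% | 0.97 to 0.67 |
| 20% | 7.72% | 8.32% | 1.93 to 1.33 |

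The range is about 0.3 to 1.9 points. If p_pre equalled p_post there would be no gap.

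**Step 2: a narrower set of assumptions**

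With women spread evenly over ages 45–79, 5/35 = 14.3% are aged 45–49. If 50–80% of these are premenopausal, s is about 7–11%. With p_pre = 0.5–2%:
- 0.93 × 9.65 + 0.07 × 2 = 9.11%
- 0.89 × 9.65 + 0.11 × 0.5 = 8.64%

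The gap is 0.54 to 1.01 points. Among an assumed 900 women, the number of premenopausal women labelled OP runs from 900 × 0.07 × 0.005 = 0.3 to 900 × 0.11 × 0.02 = 2.0.

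**Step 3: the all-resident target**

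If premenopausal women stay in the denominator, the alternative is to count none of them as a T-score case. The rule as written then adds s × p_pre to the female figure. At s = 10% and p_pre = 3% this is 0.30 points (8.99% against 8.69%). Over the full range it is 0 to 0.20 × 3 = 0.6 points, always upward.

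**Step 4: both sexes together**

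With half men, the overall figure is 7.90–8.70% with premenopausal women included and 8.78–8.84% without. The gap is about 0.1 to 0.9 points.

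**Step 5: against sampling error**

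Half-width of the 95% interval = 1.96 × √(p(1 − p)/n).
- Women only, p = 9.65%: 2.1 points at n = 750, 1.9 points at n = 900 (both numbers assumed).
- Whole sample of 1,500, p = 8.08–9.65%: 1.4–1.5 points.

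The female gap therefore runs from negligible to about one half-width.

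**Step 6: make-up of the female comparison groups**

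At s = 10% and p_pre = 3%:
- premenopausal share of OP women = 0.10 × 3 / 8.985 = 3.3%
- premenopausal share of non-OP women = 0.10 × 97 / 91.015 = 10.7%

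Under these values, premenopausal women sit disproportionately in the non-OP group.

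**The case against.** Five points can be made on the other side.

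- **The text does not say that the T-score is invalid before menopause.** This is correct, and a reader might infer it. The Introduction only shows whom one cited study reported on. Any limit in the cited WHO and Chinese guidance cannot be seen from here, so the point does not rest on invalidity. It rests on mixing two groups that the benchmark keeps apart.
- **That the rule applies to everyone is an inference.** The article defines no prevalence denominator, and a full protocol or analysis plan may do so. This weakens the point without removing it. The case definition is printed here without a limit, and someone following it would pool the women.
- **The stated target is community residents aged 45–80.** Premenopausal women in that range belong in its denominator. A reader might infer that including them dilutes prevalence. That holds only against a postmenopausal-only figure, which the article does not name as its target. For the stated target, Step 3 shows a small rise instead. No net bias in one direction is established.
- **The size rests on assumptions.** This is true throughout. Few women would carry a doubtful OP label, and those with T between -1 and -2.5 are osteopenic and never enter OP prevalence.
- **Menopausal age is undefined for premenopausal women under any cut-off.** Also true, because it follows from enrolling them. It still means that an analysis of that factor needs a stated population.

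The adjustment factors are given as examples, so adding menopausal status is not ruled out.

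**Conclusion.** The point holds as one of interpretability and comparability, and it is worth changing. Followed as printed, the rule yields a female prevalence that blends premenopausal and postmenopausal women in a proportion set by who volunteers. It also yields a risk-factor comparison with the same mixture. The female result could not be read against the postmenopausal figure the article cites.

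Under the assumed ranges (5–20% premenopausal, 0–3% of them with T ≤ -2.5, 9.65% in postmenopausal women), the pooled female figure differs from a postmenopausal-only figure by about 0.3–1.9 points. The lower end is negligible, and the upper end is about one sampling half-width among women. The all-resident figure would be raised slightly, if at all. The document supplies neither the premenopausal share nor their T-score distribution, so these are illustrations and not estimates of bias.

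**What to change.** Reconcile Diagnostic Criteria, Inclusion and Exclusion Criteria, Bone Density Screening and Collecting Clinical Information as follows.

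1. Use the recorded menstrual status to define the set for T-score-based OP prevalence and for the OP versus non-OP risk-factor comparison: postmenopausal women and men aged 50 or over.
2. Report premenopausal women as a separate stratum, using the Z-values already recorded.
3. State in advance to which stratum perimenopausal women are assigned.
4. If a figure for all residents aged 45–80 is also wanted, as the stated aim suggests, give it alongside with its denominator and its rule for premenopausal women written out.
5. Keep all women in the continuous-BMD analyses and the fracture follow-up.

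No new data are needed and nobody leaves the study. Item 1 changes which prevalence figure leads, so the wording of the aim should be brought into line. The female denominator for that figure shrinks by the premenopausal share. With an assumed 750 women and 5–20% premenopausal, it falls to about 712–600, and the half-width at 9.65% rises from 2.1 to about 2.2–2.4 points.

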### Biochemical Indicators of Bone Metabolism Testing

The bone metabolism indicators we will measure will include blood calcium, phosphorus, magnesium, creatinine, alkaline phosphatase, thyroid stimulating hormones, 25-hydroxyvitamin D3, and osteocalcin. Additionally, bone turnover markers, including procollagen type 1 N-terminal propeptide (P1NP) and the β cross-linked C-telopeptide of type 1 collagen (β-CTX), will be determined by electrochemiluminescence.

For each subject, 7 ml peripheral venous blood will be collected in fasting conditions between 8 a.m. and 9 a.m. on the day of physical examination. The anticoagulant vacuum blood collection tube will be 1 ml and the two procoagulant vacuum blood collection tubes will be 3 ml. The Guangzhou KingMed Diagnostics Limited Liability Company is responsible for collecting and testing blood samples.

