### Data Management and Statistical Analysis

Data will be recorded in the case report form (CRF), and it will be reviewed and validated by researchers, data managers, and statisticians for final statistical analysis at the end of this study. The CRF will be entered into Epidata 3.1 software by two researchers independently, and the recorded data will be checked for consistency. If there are inconsistencies, the CRF or other original records will be carefully verified. The data will be modified one by one until the independently entered data are identical. The data administrator will further check the exported database and use a logic check to check data until and doubts are resolved. The electronic database will eventually be locked.

IBM SPSS version 22.0 (SPSS, Chicago, IL, United States) software will be used to analyze the data. Continuous data will be analyzed using the independent *t*-test or Wilcoxon's rank sum test, while categorical data will be compared using the chi-square or Fisher's exact test. All statistical analysis tests will be performed using a two-sided hypothesis test. The *P* ≤ 0.05, and the difference in the test will be considered statistically significant. We will also adjust the correlation analyses for factors such as age, gender, and comorbidities.

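### OP is classified by current T-score alone and treated participants are enrolled, so treated, previously diagnosed OP now above -2.5 counts as non-OP; this can understate prevalence and contaminate the comparison group and bone-marker results

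*Protocol article*

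**What the plan says.** All references are to the protocol article.

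- **Diagnostic Criteria.** Everyone is placed in one of three groups by T-score. The only route to an OP classification is the last cut-off: "T-score ≤-2.5 is considered OP based on bone densitometry". The cut-offs are attributed to the WHO and to the "Chinese guidelines for the diagnosis and treatment of primary OP".
- **Inclusion and Exclusion Criteria.** Entry depends on length of residence, age and consent. The exclusions are "Participants who suffer from mental illness, such as a mental deficiency, memory or thinking disorder" and those "who are unable to cooperate with investigators due to disability or lack of physical capacity will be excluded". Treatment for OP is not mentioned.
- **Collecting Clinical Information.** The questionnaire covers "history of previous illness and medication". The article describes no use of this item in classifying OP.
- **Biochemical Indicators of Bone Metabolism Testing.** P1NP and β-CTX are measured, with no provision for participants on treatment.
- **Data Management and Statistical Analysis.** "We will also adjust the correlation analyses for factors such as age, gender, and comorbidities". Medication is not named, although the list is open-ended.

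**The concern.** Anti-osteoporosis treatment is given because of OP, and it acts on both the T-score that defines the case and the turnover markers studied as correlates. A rule that looks only at today's T-score therefore treats a successfully treated case as a non-case. Three results are exposed:

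- **Prevalence of OP**, a stated aim. Any error from this source is downward.
- **Risk-factor comparisons.** Some true cases sit in the non-OP group. If treatment is more common among people with the factor (older, or with a previous fracture, say), their cases are missed more often and the association is altered.
- **P1NP and β-CTX comparisons.** Values altered by drugs are pooled with untreated values, so a difference between groups may reflect treatment rather than disease.

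Covariate adjustment acts on the predictor side of a model. It does not move a participant from the wrong outcome group to the right one.

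**Working it through.** **Is there a plan figure to reproduce?** Not on this point. The sample size of at least 1,500 is attributed to a power analysis whose inputs are not given, and the concern does not depend on it.

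**Step 1: apply the rule as written.** Take a resident with diagnosed OP, on treatment, whose T-score is now -2.3. Nothing in the eligibility section excludes this person. The Diagnostic Criteria place -2.3 between -2.5 and -1, so the person is recorded as osteopenic. No other section changes that.

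**Step 2: effect on prevalence.** Inputs:

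- p = true prevalence. 9.65% (postmenopausal women) and 8.08% (elderly men) come from the study of another region cited in the Introduction. They are illustrations only. That study also used WHO criteria, so nothing shows that its figures include treated people above -2.5.
- t = share of OP cases treated: 5-30%, assumed.
- u = share of treated cases now above -2.5: 25-50%, assumed.
- n = 1,500, from Materials and Methods.

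Observed prevalence = p(1 - t·u). Cases missed = n·p·t·u.

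| p | t | u | Observed | Understated by | Missed per 1,500 |
|---|---|---|---|---|---|
| 9.65% | 5% | 25% | 9.53% | 0.12 points | 1.8 |
| 9.65% | 10% | 50% | 9.17% | 0.48 points | 7.2 |
| 9.65% | 30% | 50% | 8.20% | 1.45 points | 21.7 |
| 8.08% | 5% | 25% | 7.98% | 0.10 points | 1.5 |
| 8.08% | 30% | 50% | 6.87% | 1.21 points | 18.2 |

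For example, 9.65% × (1 - 0.30 × 0.50) = 8.20%.

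For scale, the 95% half-width at n = 1,500 is 1.96 × √(0.0965 × 0.9035 / 1,500) = 1.49 points. Only the top of the assumed range approaches this sampling error.

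**Step 3: effect on an odds ratio.** Assume a factor carried by 30% of participants, a true odds ratio of 2.0 and p = 9.65%. Solving 0.7·p0 + 0.3·p1 = 0.0965 with that odds ratio gives p0 = 7.68% (unexposed) and p1 = 14.26% (exposed). Multiply each by the share of cases not missed and recompute the odds ratio.

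| Missed, unexposed | Missed, exposed | Observed odds ratio |
|---|---|---|
| 5% | 5% | 1.99 |
| 15% | 15% | 1.98 |
| 5% | 15% | 1.75 |
| 5% | 30% | 1.41 |

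In the third row, for example, the exposed risk becomes 0.1426 × 0.85 = 0.1212 and the unexposed risk 0.0768 × 0.95 = 0.0729. The odds ratio is (0.1212/0.8788) / (0.0729/0.9271) = 1.75.

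The last row is extreme. It misses (0.05 × 0.0537 + 0.30 × 0.0428) / 0.0965 = 16% of all cases, slightly above the 15% maximum of t·u in Step 2. The third row misses 9% overall, within that range.

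No arithmetic is offered for the bone markers, because the article gives no values to work from.

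**The case against.** The strongest reply is that T-score prevalence is a legitimate quantity, that the cut-offs are the published ones, and that a condensed article may leave the handling of treated participants to a fuller document. The medication history is collected and the adjustment list is open, so the article shows only that no use of the history is described, not that none is planned. This stands in part. The T-score figure should be kept, and detailed model specification is not at issue. But the case definition and eligibility list are stated in the article, and followed as written they produce the misclassification.

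Four stronger readings are tempting and are not supported:

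- A reader might infer that using a guideline for primary OP contradicts enrolling people with secondary causes. The word belongs to the guideline's title; the aim is OP in community residents, with no restriction to primary disease.
- A reader might infer that treated or secondary cases should be excluded. That would make the prevalence sample less representative, and dropping glucocorticoid users or secondary causes would remove possible determinants from a study of risk factors.
- A reader might infer that treatment started after screening goes unrecorded. The follow-up section is one condensed sentence that does not list the annual questions. That fracture patients are asked about later treatment does not show that others are not asked about drugs.
- A reader might infer that prevalence is understated by a known amount. No treated share is given, and the Introduction describes community OP as typically undiagnosed before fracture, which suggests that the share could be low.

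**Conclusion.** The point holds as a gap in the case definition. A T-score-only rule, applied to a sample that admits people on anti-osteoporosis drugs, counts some diagnosed cases as non-cases, and adjustment for comorbidities does not repair that. For prevalence the direction is known (downward) but the size is not: about 0.1 to 1.45 points at an illustrative 9.65%, and 0.1 to 1.2 points at 8.08%, entirely under the assumed treated and reclassified shares. It may be negligible if few participants are treated. For risk factors the bias is trivial when treatment is unrelated to the factor (2.0 becomes 1.98-1.99) and material when it is related (for example 1.75). Its direction cannot be stated for every factor. The bone-marker results carry a risk of contamination that cannot be quantified from the article. Because the remedy is cheap and rests on information already being gathered, the change is worth making.

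**What to change.** Using the illness and medication history in the questionnaire:

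1. Report prevalence twice: by T-score at or below -2.5 alone, and by T-score at or below -2.5 or current anti-osteoporosis treatment for previously diagnosed OP. State both definitions in the analysis text.
2. In the risk-factor and bone-marker analyses, put participants on anti-osteoporosis treatment in a separate stratum, or repeat the analyses without them as a sensitivity analysis.
3. Keep glucocorticoid use and secondary causes in the models as candidate risk factors; do not exclude them.
4. Report how many participants are on treatment and how many of those are above -2.5, so that readers can judge the size directly.

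Before relying on this, confirm that the questionnaire, which the article does not reproduce, records current use and the earlier diagnosis. The second prevalence figure rests on self-report, and the Discussion already concedes recall bias there; this is a reason to show both figures. The cost is a few lines of analysis text, one extra prevalence figure and slightly fewer participants in the untreated risk-factor models. Clinical management is unaffected.
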